### 4.3 Open label treatment phase

If angiomyolipoma progression (as defined in [Section 7.5.2](#)) is documented by central radiology review or an angiomyolipoma-related bleeding of grade 2 or worse (NCI CTCAE, version 3.0) during the blinded treatment phase, then the treating physician may proceed to unblind the patient. Central radiology review of the CT/MRIs will be completed no later than 3 weeks after receipt by the central reviewer, so the unblinding may not be able to take place until up to 3 weeks after the progression was actually observed. However, if progression was unequivocal according to the local radiologist, then the investigator should contact the Novartis Clinical Trial Head (CTH) or designee to proceed with unblinding without waiting for confirmation from central radiology review.

Following unblinding, patients who had been receiving placebo may be offered open-label treatment with RAD001 if the treating physician believes the patient could benefit from this therapy.

For the open-label phase of the study, the most recent kidney CT/MRI from the blinded treatment phase of the study will be used as the baseline, and further kidney CT/MRIs will be conducted at 12, 24 and 48 weeks after the start of open-label RAD001, and annually thereafter, until angiomyolipoma progression, unacceptable toxicity or discontinuation for any other reason. An additional CT/MRI of the kidney will be obtained at End of Treatment in the open-label RAD001 phase, provided discontinuation was not for angiomyolipoma progression and if it had been more than 8 weeks since the most recent CT/MRI of the kidney during the

first year of open-label treatment or more than 6 months since the most recent CT/MRI thereafter. For each patient, the same imaging modality should be used throughout the trial. All kidney imaging scans obtained in the open-label phase of the trial will be sent in for central radiological review within 2 days of the scan.

Patients receiving open-label treatment with RAD001 will continue having safety and efficacy assessments as in the blinded treatment phase, as described in the Visit Evaluation Schedule provided in [Table 7-2](#), with the exception of biomarker and pharmacokinetic assessments which will not be performed in the open-label phase.

Open-label treatment with RAD001 will continue until the patient again presents with angiomyolipoma progression (second occurrence) which is either radiologically documented or is an angiomyolipoma-related bleeding of grade 2 or worse (NCI CTCAE, version 3.0). At this point, the patient will be discontinued from the study and will enter the follow-up phase.

The investigator or his/her designee will **not** disclose patient unblinding information to the central radiology reviewers. Due to the unblinding of a subset of patients upon angiomyolipoma progression, members of the Novartis clinical trial team may become unblinded to an individual patient's treatment during the conduct of the trial including team members involved in source data verification. The blinding of the central radiology review, the basis for the primary analysis of the primary endpoint of the trial, will be maintained despite the planned unblinding.

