#### **4.5 Extension phase**

There are two distinct parts of this trial, the core and extension phase. The core phase is from the start of the trial up to the time when the results of the final primary analysis are known. This primary analysis will be performed using all data up to the data cutoff date, which is defined as 6 months after the last patient is randomized. Following a database freeze, the statistical analysis will be performed. During this time, patients will continue on the blinded treatment phase or open-label phase as before, until the time when the results of the final data analysis are known and the core phase of the trial is terminated.

If this final data analysis fails to show superiority of RAD001 over placebo, all patients will be discontinued from the study and will have end of treatment evaluations as indicated in [Table 7-1](#) and [Table 7-2](#). In this case there will be no extension phase.

If the final trial results favor RAD001, then an extension phase will be launched. All patients still receiving study treatment at this time, as well as those being followed for post-treatment evaluation, will be given the option of starting open-label RAD001. Similarly, patients receiving open-label RAD001 at the end of the core phase will be offered to continue into the extension period. The extension phase will run until 4 years after the last patient was randomized, ensuring patient follow-up of 4-5 years (assuming patient accrual over a period of approximately 12 months).

Those patients entering the extension phase, who had previously only been receiving placebo, will have scheduled assessments beginning at Treatment Day 1 according to [Table 7-2](#). Patients that had been on active RAD001 prior to beginning the extension phase will simply continue their sequence of assessments, according to [Table 7-1](#) and [Table 7-2](#). Accordingly, patients that had been on active RAD001 in the Open-label phase prior to beginning the extension phase will simply continue their sequence of assessments according to [Table 7-2](#). Patients in the extension phase will continue to have the same safety and efficacy assessments as in the core phase until angiomyolipoma progression, with the exception of biomarker assessments and pharmacokinetic assessments which will not be performed in the extension phase.

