## **7.5 Efficacy**

### **7.5.1 Radiological evaluation**

For instruction regarding baseline assessments of angiomyolipomata, please refer to [Table 7-1](#) and [Section 7.3](#).

The same method of assessment and the same technique should be used to characterize each identified and reported angiomyolipoma at baseline, at 12, 24 and 48 weeks, and annually thereafter.

Each center must have a designated radiologist or other physician who is responsible for the interpretation of CT scan or multiphase MRI. The same radiologist/physician should perform the evaluation for the entire duration of the study. All radiology evaluations will be performed initially by the local radiologist, but designation of response and progression will be based only on the evaluations made by the Independent Central Radiology Review. CT/MRIs must be digitized and sent to central radiology within 2 days of the scan date. Following receipt of each scan, the Independent Central Radiology Review will be completed and the results will be communicated back to the participating center within 3 weeks.

The presence or absence of polycystic kidney disease will be documented at baseline by the central reviewer.

If an initial observation of angiomyolipoma response is made, a confirmation scan should be obtained approximately 12 weeks after the initial observation (and no sooner than 8 weeks later).

All patients being discontinued from the study for angiomyolipoma progression must have their progression documented using the criteria specified in Section 7.5.2. In particular, a discontinuation reason of “angiomyolipoma progression” will not be sufficient to establish that angiomyolipoma progression actually occurred.

All patients who are participating in the non-interventional follow-up phase, a kidney CT/MRI scan should be obtained after 1-year of the last dose of study treatment or prior to the initiation of an intervention. Please refer to [Table 7-3](#) and [Section 4.6](#).

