### **Angiomyolipoma response assessment:**

**Angiomyolipoma response** will be defined as:

- a reduction in angiomyolipoma volume of at least 50% relative to baseline, where angiomyolipoma volume is the sum of the volumes of all target angiomyolipomata identified at baseline, and confirmed with a second scan performed approximately 12 weeks later (and no sooner than 8 weeks later).

In addition, angiomyolipoma response requires satisfying all of the following criteria:

- no new angiomyolipomata  $\geq 1.0$  cm in longest diameter are identified
- neither kidney increases in volume by more than 20% from nadir (where nadir is the lowest kidney volume obtained for the patient, separately for each kidney, previously in the trial including baseline)
- the patient does not have any angiomyolipoma-related bleeding of grade  $\geq 2$  (as defined by NCI CTCAE, version 3.0).

**Angiomyolipoma progression** will be defined as one or more of the following:

- an increase from nadir of 25% or more in angiomyolipoma volume to a value greater than baseline (where angiomyolipoma volume is the sum of the volumes of all target angiomyolipomata identified at baseline and where nadir is the lowest angiomyolipoma volume achieved by the patient previously in the trial (including baseline))
- the appearance of a new angiomyolipoma  $\geq 1.0$  cm in longest diameter
- an increase from nadir of 20% or more in the volume of either kidney to a value greater than baseline, where nadir is the lowest kidney volume obtained for the patient, separately for each kidney, previously in the trial (including baseline)
- angiomyolipoma-related bleeding grade  $\geq 2$  as defined by NCI CTCAE, version 3.0.

**Note:** In some instances, disease that is measurable as a target lesion at baseline and appears to be one mass can split to become two or more smaller sub-lesions. When this occurs, the image review system allows the central reviewer to identify the separate sub-lesions as unique and non-overlapping so that the volume of each sub-lesion can be determined. The combined volumes of the sub-lesions will be reported as the volume of the lesion that has split. The individual split lesions will not be considered as new lesions, and will not automatically trigger an angiomyolipoma progression.

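### Section 4.3 restarts the baseline for placebo patients who start open-label RAD001, but the nadir in Section 7.5.2 still reaches back into the placebo period, so some patients begin with no growth margin before a mandatory stop

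*Protocol*

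**What the plan says.** Protocol Section 4.3 sets a new reference scan for patients unblinded to placebo and offered RAD001: "the most recent kidney CT/MRI from the blinded treatment phase of the study will be used as the baseline". The notes to Table 7-2 likewise take the baseline visit from the end of the blinded phase.

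Section 7.5.2 holds the only progression rule that governs study treatment. For target volume it requires a rise of at least 25% from nadir to a value above baseline, "where nadir is the lowest angiomyolipoma volume achieved by the patient previously in the trial (including baseline". For kidney volume it requires "an increase from nadir of 20% or more in the volume of either kidney to a value greater than baseline", with the nadir again running over the whole trial, separately for each kidney. Neither section restarts the nadir at crossover.

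The consequence is fixed in Section 4.3: "Open-label treatment with RAD001 will continue until the patient again presents with angiomyolipoma progression (second occurrence"), after which the patient is discontinued and goes to follow-up. Section 4.5 also lists progression among the reasons for stopping RAD001 in the extension.

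Section 10.5.11 states that it uses the Section 7.5.2 definition, but words the nadir as the lowest value in the everolimus period, counting the value just before everolimus began. That section covers only the analysis after everolimus is stopped.

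**The concern.** Progression is a two-part test: enough growth from nadir, and a value above baseline. Section 4.3 moves the second reference point and leaves the first in the placebo period. A patient who crossed over because a volume criterion was met has already passed the from-nadir part on the day open-label treatment starts. Only the above-baseline part remains, and it has no percentage attached.

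At stake is whether a patient who has just started active drug may stay on it. Section 7.5.2 asks for a confirmatory scan for response but states none for progression, so one reading slightly above the open-label baseline could end treatment. Open-label progression data would also mix patients judged against different effective thresholds.

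**Working it through.** The protocol gives no figure on this point to reproduce, so the check applies its rule directly.

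**Inputs**
- B = open-label baseline, the last blinded scan (Section 4.3).
- N = lowest value in the placebo period (Section 7.5.2), so N ≤ B.
- m = lowest value so far on open-label drug; before any shrinkage, m = B.
- k = 1.25 for target volume and 1.20 for kidney volume (Section 7.5.2).
- Percentage falls at 12 months: Section 1.4.6.
- The volumes in mL are illustrative; the protocol gives none.

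**Formulas for the progression threshold**
- As written: max(k × min(N, m), B).
- With the nadir also restarted: max(k × min(B, m), B).

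**1. Last blinded scan already met the volume criterion (B ≥ kN).** As min(N, m) ≤ N, the first term never exceeds kN ≤ B. The threshold is B on entry and stays at B.
- Target, N = 100, B = 126, no shrinkage: max(125, 126) = 126, a margin of 0%. Restarted: 1.25 × 126 = 157.5, a margin of 25%.
- Kidney, N = 400, B = 490, no shrinkage: max(480, 490) = 490, a margin of 0%. Restarted: 1.2 × 490 = 588, a margin of 20%.

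**2. When the two rules agree in that group.** The restarted threshold drops to B when k × m ≤ B, that is, after a fall of 1 − 1/1.25 = 20.0% (kidney 1 − 1/1.2 = 16.7%).

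**3. Phase II falls in target volume.** Section 1.4.6 has 12-month data on 9 of 17 treated patients. With N = 100 and B = 126:
- 10 mg: falls of 61.7%, 60.2%, 60.1% and 27.4% exceed 20%, so there is no difference. The fifth fell 12.8%: m = 126 × 0.872 = 109.9. Thresholds are 126 as written and 1.25 × 109.9 = 137.3 restarted. Room to regrow from the low is 126/109.9 − 1 = 14.7% instead of 25%.
- 5 mg: falls of 67.5%, 64.4% and 39.4% give no difference. The fourth fell 18.4%: m = 126 × 0.816 = 102.8. Thresholds are 126 and 128.5, and the room is 1/0.816 − 1 = 22.5% instead of 25%.

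**4. Kidney volume in the same patients.** The lesion share of the kidney is not given. Assume share s, with other tissue unchanged, so that kidney fall = s × lesion fall. Reaching 16.7% needs:
- s = 16.67/60.1 = 27.7% for a 60.1% lesion fall;
- s = 16.67/27.4 = 60.8% for a 27.4% fall;
- s = 16.67/12.8 = 130% for a 12.8% fall, which is impossible.

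For example, with a 60.1% lesion fall and s = 20%, the kidney falls 12.0%: m = 490 × 0.8798 = 431.1. Thresholds are 490 as written and 1.2 × 431.1 = 517.3 restarted. At s = 30% the kidney falls 18.0% and the rules agree.

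**5. Last blinded scan below the volume criterion (r = B/N < k).** This covers entry on a new lesion or bleeding. It also covers a local radiologist's call that central review did not confirm, because Section 4.3 allows the investigator "to proceed with unblinding without waiting for confirmation from central radiology review". The entry margin is k/r − 1, and the rules agree after a fall of 1 − 1/r. For target volume:

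| r | Margin as written | Margin restarted | Rules agree after a fall of |
|---|---|---|---|
| 1.00 | 25% | 25% | 0% |
| 1.05 | 19.0% | 25% | 4.8% |
| 1.10 | 13.6% | 25% | 9.1% |
| 1.20 | 4.2% | 25% | 16.7% |

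For kidney volume at r = 1.10 the margin is 1.2/1.1 − 1 = 9.1% instead of 20%.

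**The case against.** The best defence is that a restarted nadir was plainly meant. The nadir window in Section 7.5.2 is said to include baseline, which fits a window that begins there; on the literal reading the open-label baseline falls inside its own nadir window. Section 4.3 speaks of the patient progressing again, whereas the literal reading lets the first episode of growth count twice. Section 10.5.11 presents its everolimus-period nadir as a restatement of Section 7.5.2. The imaging charter, which is not shown, may also settle the matter.

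Most of this stands as evidence of intent. It does not change the rule that sites and central review are given. The whole-trial window is express wording, not silence, and Section 10.5.11 does not govern stopping treatment.

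It is also fair that the effect is narrow. All nine phase II patients with 12-month data shrank, and even the weakest 10 mg responder had some room to regrow. That limits the weight of the point. Those are 12-month figures, though, while the first open-label scan is at 12 weeks, for which no volumes are given.

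A reader might infer that stable patients would be stopped. They would not: the value must exceed the open-label baseline. A reader might also infer that every crossover patient starts with no margin. That holds only for those whose last centrally read blinded scan met a volume criterion.

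**Conclusion.** The point holds as a mismatch between two stated rules, and it should be corrected. A patient whose last centrally read blinded scan was at least 25% (target) or 20% (either kidney) above the placebo-period nadir has a margin of zero on entry, where a restarted nadir would give 25% or 20%. The difference disappears after a fall of 20% (kidney 16.7%). Patients with less placebo-period growth keep a reduced margin, and those with none keep the full one.

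The consequence is confined to individual treatment continuation and open-label progression data. It concerns a probably small subset of the 33 planned placebo patients, whose number cannot be derived from the protocol. A reader might infer a stated rate of wrongful stops, but the protocol gives neither measurement variability nor early on-drug volumes, so no frequency or timing can be claimed. Nor does the defect reach the randomised comparison: time to angiomyolipoma progression counts the first progression, and the primary endpoint, power and alpha do not use the open-label rule.

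The conclusion rests on reading Section 7.5.2 as worded. The kidney illustration also rests on an assumed lesion share. For patients who first receive RAD001 in the extension, the baseline restart is less explicit: Section 4.5 says "Those patients entering the extension phase, who had previously only been receiving placebo, will have scheduled assessments beginning at Treatment Day 1" of Table 7-2, which concerns the visit schedule.

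**What to change.** Add one sentence to Sections 4.3 and 7.5.2: for a patient first starting RAD001 in the open-label or extension phase, both baseline and nadir, for target volume and for each kidney, are taken from the last scan before RAD001 onward. This matches the wording already in Section 10.5.11 and removes the doubt about extension starters.

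Apply it without revealing treatment assignment to the central readers, since Section 4.3 forbids the investigator to "disclose patient unblinding information to the central radiology reviewers". Section 7.5.1 says that "designation of response and progression will be based only on the evaluations made by the Independent Central Radiology Review", and the protocol describes no separate step that turns central volumes into progression. The cost is therefore the added text plus aligning the central review procedure with it. No new scans or data are needed.

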#### **4.4 Follow-up phase**

All patients will have a follow-up visit scheduled 4 weeks (28 days) after the last dose of study treatment to capture AEs and SAEs that may have occurred after discontinuation from the study treatment. Beyond these 28 days, any serious adverse events that are suspected to be related to the study drug and occur within the next 8 weeks (56 days) will also be collected. Medications/therapies given to the patient in treatment of SAEs during the 8 weeks after study treatment discontinuation must be recorded on the Concomitant Medications/Significant Non-Drug Therapies CRF, unless the patient begins a non-study anti-angiomyolipoma therapy, at which time collection of SAEs, AEs and concomitant medications will cease. Patients without angiomyolipoma progression at the time of discontinuation of study treatment will be followed with CT/MRI tumor assessments annually until eventual angiomyolipoma progression, the start of any non-study systemic anti-angiomyolipoma therapy, withdrawal of consent, or until end of the study, whichever occurs first. During this follow up period, the site will continue to send CT/MRIs for central review, and use of non-study systemic anti-angiomyolipoma therapies will be recorded.

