- All patients will have a follow-up visit 4 weeks (28 days) after the last dose of the study treatment. During this visit, AE and SAE information will be collected and recorded on the appropriate CRFs. Patients will also be followed for an additional 8 weeks (56 days) for collection and recording of any SAEs that are suspected to be related to study drug. In addition, any medication/therapy taken during these 8 weeks (56 days) will be recorded on the **Concomitant medications/Significant non-drug therapies CRF page**. If the patient is unable to return to the clinic, the investigator or his/her designee will contact the patient or caregiver via telephone to collect this information.
- All patients who are discontinued from study treatment for any reason other than angiomyolipoma progression will continue to have kidney CT/MRIs performed annually until eventual angiomyolipoma progression, the start of any non-study systemic anti-angiomyolipoma therapy, withdrawal of consent, or until end of the study, whichever occurs first. Radiological studies will be sent for central review during this follow-up period. The investigator or his/her designee will collect information on the initiation of additional anti-angiomyolipoma therapies every month. This information may be obtained during a telephone call and will be recorded in the source documents as well as on the Non-Study Systemic Anti-angiomyolipoma Therapy CRF page.

All patients must have evaluations for 4 weeks (28 days) after the last dose of study treatment (and an additional 8 weeks (56 days) for collection and recording of any SAEs that are suspected to be related to study drug). Patients lost to follow up should be recorded as such on the End of Treatment CRF. Patients who require angiomyolipoma-related surgery should discontinue the study drug before the surgery. Patients who discontinue study drug before completing the study should be scheduled for a visit as soon as possible, at which time all of the assessments listed for End of Treatment visit will be performed. At a minimum, all

patients who discontinue study treatment, including those who refuse to return for a final visit, will be contacted for safety evaluations at 12 weeks (84 days) after the last dose of study drug.

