### 7.8.1

## 8 Safety monitoring

### 8.1 Serious adverse event reporting

To ensure patient safety, every SAE, **regardless of suspected causality**, occurring after the patient has provided informed consent and until 4 weeks after the patient has stopped study treatment/participation must be reported to Novartis within 24 hours of learning of its occurrence. Any SAEs experienced after this 4-week period (**for up to 12 weeks (84 days)**) should only be reported to Novartis if the investigator suspects a causal relationship to the study drug. Recurrent episodes, complications, or progression of the initial SAE must be reported as follow-up to the original episode within 24 hours of the investigator receiving the follow-up information. An SAE occurring at a different time interval or otherwise considered completely unrelated to a previously reported one should be reported separately as a new event.

Information about all SAEs is collected and recorded on the Serious Adverse Event Report Form. The investigator must assess and record the relationship of each SAE to each specific

study drug (if there is more than one study drug), complete the SAE Report Form in English, and send the completed and signed form by fax within 24 hours to the local Novartis Integrated Medical Safety.

The telephone and fax number of the contact persons in the local department of Pharmacovigilance Operations, specific to the site, are listed in the investigator folder provided to each site. The original copy of the SAE Report Form and the fax confirmation sheet must be kept with the CRF documentation at the study site.

Follow-up information is sent to the same person to whom the original SAE Report Form was sent, using a new SAE Report Form stating that this is a follow-up to the previously reported SAE and giving the date of the original report. Each recurrence, complication, or progression of the original event should be reported as a follow-up to that event regardless of when it occurs. The follow-up information should describe whether the event has resolved or continues, if and how it was treated, whether the blind was broken or not, and whether the patient continued or withdrew from study participation.

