### 10.4.1 Variable

The primary endpoint of this study, angiomyolipoma response rate, is defined as the proportion of patients with an angiomyolipoma response, as defined in [Section 7.5.2](#), using data from the Independent Central Radiological Review of CT/MRIs and the Adverse Events CRF page (to identify angiomyolipoma-related bleeding of grade 2 or worse as defined by NCI CTCAE version 3.0).

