### 10.5.11 Evaluation after everolimus discontinuation

Patient who discontinue everolimus for reasons other than angiomyolipoma progression, and who subsequently do not receive systemic treatment with an mTOR inhibitor, will be analysed specifically. Data included in this analysis will be data from the follow-up phase (until the end of the extension phase) and/or from the non-interventional follow-up phase.

Reasons for everolimus discontinuation and for non-inclusion in the non-interventional follow-up phase will be presented for this population. A table of demographic characteristics at start of everolimus and duration of everolimus treatment will be produced in order to appreciate the selection biases.

Sum of volumes of target angiomyolipoma lesions (the ones identified before the start of everolimus) will be described at the time of everolimus discontinuation (end of treatment visit or non-interventional follow-up entry visit) and at the time of the one-year follow-up scan (i.e. scan performed one year after everolimus discontinuation), or an earlier scan which was performed following an angiomyolipoma-related bleeding event ( $\geq$  grade 2), or prior to any intervention such as the start of systemic mTOR treatment, embolization or nephrectomy.

The effect of stopping everolimus on tumor growth will be described in terms of change and percentage change in the sum of the angiomyolipoma target lesions volume from the start of everolimus and from the time of everolimus discontinuation (scan performed at the end of everolimus treatment). Individual plots of sum of volumes of target angiomyolipoma lesions by time will also be performed to illustrate the tumor evolution after stopping everolimus. Similar analyses will be conducted to describe the changes in kidney volume.

The number of patients with at least one new angiomyolipoma lesion  $\geq 1.0$  cm in longest diameter and one angiomyolipoma-related bleeding of grade  $\geq 2$  assessed at the one-year follow-up scan will be tabulated.

If the number of patients included in this analysis is sufficient, the angiomyolipoma progression rate one year after everolimus discontinuation will be provided with exact 95% confidence intervals (Clopper and Pearson 1934). The angiomyolipoma progression will be defined as in Section 7.5.2 of the protocol, i.e. one or more of the following criteria should be observed at the one-year follow-up scan:

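### Angiomyolipoma-related bleeding counts as progression, but in the follow-up phase all-cause collection of it ends 28 days after the last dose, unlike in the non-interventional phase

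*Protocol*

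**What the plan says.** **Endpoint.** Protocol section 7.5.2 lists "angiomyolipoma-related bleeding grade" 2 or worse among four criteria, any one of which is progression. For the primary endpoint, section 10.4.1 names the source as "the Adverse Events CRF page (to identify angiomyolipoma-related bleeding of grade 2 or worse". Section 10.5.1 uses the same progression definition for TTAP. It censors at the data cut-off, the start of a non-study systemic therapy, or death, and does not censor at treatment discontinuation.

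**Follow-up phase.** Section 4.4 states: "All patients will have a follow-up visit scheduled 4 weeks (28 days) after the last dose of study treatment to capture AEs and SAEs". For the following 56 days only serious events suspected to be drug-related are collected. Section 8.1 agrees: after the first four weeks, serious events "should only be reported to Novartis if the investigator suspects a causal relationship to the study drug". Section 4.4 also lets collection stop sooner if a non-study anti-angiomyolipoma therapy begins. Efficacy follow-up runs on: "Patients without angiomyolipoma progression at the time of discontinuation of study treatment will be followed with CT/MRI tumor assessments annually until eventual angiomyolipoma progression". Under section 6.7.4 the site "will collect information on the initiation of additional anti-angiomyolipoma therapies every month"; bleeding is not mentioned there.

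**Off-treatment analysis.** Section 10.5.11 begins its data definition with "Data included in this analysis will be data from the follow-up phase (until the end of the extension phase" and names the non-interventional phase as the other source. It tabulates grade 2 or worse bleeding and, if numbers allow, a progression rate that includes it.

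**Non-interventional phase.** Section 4.6 obliges patients to report angiomyolipoma-related bleeding to the site, and footnote e of Table 7-3 sends it to the CRF whatever its cause.

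**The concern.** A bleed of grade 2 or worse is progression with no scan needed. A patient who stops treatment without progression stays at risk for TTAP, so a bleed before the cut-off is an event. The safety window was evidently written for drug toxicity. It filters on seriousness and suspected causality, and neither filter belongs to the endpoint definition.

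A site that follows the stated window correctly could therefore leave an endpoint event unrecorded. TTAP is the first secondary endpoint in the closed testing procedure (10.5.3). In 10.5.11, the absence of a recorded bleed would mean that bleeding was asked about and absent in one source, but only that it was not routinely asked about in the other. Exclusion 25 (5.2.1) bars from the non-interventional phase anyone who has already had the one-year off-drug scan. Those patients contribute follow-up-phase data only, and the later phase cannot fill the gap for them.

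**Working it through.** **1. Collection window.** 28 days all-cause + 56 days suspected-related serious events = 84 days. This reproduces the total stated in the adverse event footnotes to Tables 7-1 and 7-2.

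**2. Which bleeds (grade 2 or worse) fall inside the stated rules.**

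| Bleed | Follow-up phase, to day 28 | Days 29–84 | After day 84 | Non-interventional phase |
|---|---|---|---|---|
| Serious, drug suspected | collected | collected | outside window | collected |
| Serious, drug not suspected | collected | not collected | outside window | collected |
| Non-serious | collected | not collected | outside window | collected |

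**3. Share of a 365-day year off treatment (the horizon of 10.5.11).**
- All-cause collection: 28/365 = 7.7%. Without it: 365 − 28 = 337 days, 337/365 = 92.3%.
- Any adverse event collection at all: 84/365 = 23.0%. Without it: 365 − 84 = 281 days, 281/365 = 77.0%.

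These shares describe follow-up-phase patients only.

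**4. Window in which a TTAP event could be lost.** The cut-off is 6 months after the last randomization, and the protocol assumes 12 months of accrual, so follow-up is 6 to 18 months. At 30.4375 days per month that is about 183 to 548 days. For a patient who stops almost at once:
- beyond day 28: 183 − 28 = 155, up to 548 − 28 = 520 days;
- beyond day 84: 183 − 84 = 99, up to 548 − 84 = 464 days.

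These are upper limits. They are not event-free time credited to the patient, because 10.5.1 censors at the most recent CT/MRI.

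**5. Expected missed bleeds.** The protocol gives neither a discontinuation rate for this population nor an annual bleed rate (section 1.2 gives cumulative risks only), so these inputs are assumptions:
- k = 5 to 20 patients off treatment without progression;
- r = 1% to 5% bleeds per patient-year;
- t = 0.5 to 0.92 uncollected years each (0.92 = 337/365).

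Expected number = k × r × t.
- Low: 5 × 0.01 × 0.5 = 0.03.
- Middle: 10 × 0.03 × 0.92 = 0.28.
- High: 20 × 0.05 × 0.92 = 0.92.

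The expected count stays below one across this range.

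**The case against.** The strongest reply is that the protocol does not ignore these bleeds.

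- Follow-up runs until progression as 7.5.2 defines it, bleeding included. Section 6.7.5 lists progression as a reason for completing study evaluation, and 7.5.1 requires progression to be documented against the 7.5.2 criteria.
- Tables 7-1 and 7-2 mark serious events and concomitant medications at the study evaluation completion visit, and 6.7.4 requires a safety contact at 84 days.
- Section 7.6.1 sets 28 days as a minimum, and the synopsis asks patients to report bleeding to the site without naming a phase.

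This stands in part. A bleed that the site happens to learn of could end follow-up as progression. But none of these provisions sets up active all-cause collection of date and grade. Section 7.5.1 itself says that a discontinuation reason does not establish progression. The table footnotes narrow the mark at the completion visit, and the synopsis line leads straight into non-interventional text. So bleeds may be missed; it is not certain that they are.

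A reader might also infer three stronger things that the documents do not support.

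- **That nothing at all is collected after day 28.** Serious, suspected-related bleeds are taken to day 84.
- **That the gap lengthens TTAP on RAD001.** The 7% versus 0% discontinuation for adverse reactions in section 1.4.5 comes from metastatic renal cancer, with median treatment of 141 versus 60 days. It does not estimate discontinuation without progression here. A bleed missed after the last scan loses an event but adds no event-free time.
- **That the whole of 10.5.11 is compromised.** Only its follow-up-phase part is, and the analysis is descriptive.

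**Conclusion.** The mismatch is real: an endpoint component has no matching all-cause collection rule in one of the phases in which it counts. Bleeds after day 28 that are non-serious, or not attributed to the drug, may go unrecorded. Some TTAP events could then become censored observations, and the two sources pooled in 10.5.11 would differ in how bleeding is ascertained. An analysis plan cannot recover data that were never collected.

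The size is modest. The gap is 92% of a follow-up-phase patient's off-treatment year, but the expected loss is about 0.03 to 0.9 bleeds, given the assumed numbers off treatment and bleed rates. The direction of any bias between arms is not established, and the primary endpoint is not shown to be affected. Severity is moderate to low: an inexpensive improvement, not a must-fix.

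**What to change.** Align sections 4.4 and 6.7.4 and the adverse event footnotes to Tables 7-1 and 7-2 with section 4.6. State that angiomyolipoma-related bleeding is recorded on the Adverse Events CRF with onset date, CTCAE grade and diagnostic procedures, regardless of seriousness or suspected causality, until progression or study exit. Add a question on bleeding to the monthly contact.

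The cost is protocol wording and one more question at an existing contact, with slightly more data to collect. The CRF page exists, and no new visit or procedure is needed.
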